#### Secondary objectives

The secondary objectives include comparing clinical outcomes such as weight, body mass index (BMI), opportunistic infections (OI), Cluster Designation (CD) 4 count, viral load and quality of life between the groups. These comparisons will be performed at 3 and 6 months.

### Outcome measures

Our primary outcome will be adherence rates, measured using VAS. SR and PRD will also be used to supplement VAS (Table 1).

**Table 1 T1:** Overview of outcome measures

Outcome measures	Scale	Type	Measure	Analysis method
**Primary**				

Adherence at 6 months*				

VAS	Ordinal	Binary	VAS percentage >95%	Chi-squared test

Self report	Ordinal	Binary	% adherence in last month > 95%	Chi-squared test

PRD	Ordinal	Binary	% of complete refills >95%	Chi-squared test

**Secondary**				

Weight	Ratio	Continuous	Change in weight	T-test

BMI	Ratio	Continuous	Change in BMI	T-test

OI	Nominal	Binary	Occurrence of new OI	Chi-squared test

Mortality	Nominal	Binary	All deaths	Chi-squared test

Retention	Nominal	Binary	Number retained in care	Chi-squared test

CD4 count	Ratio	Continuous	Change in CD4 count	T-test

Viral load	Ratio	Continuous	Change in viral load	T-test

Satisfaction with care	Ordinal	Categorical	Change in satisfaction scores	T-test

QoL	Ordinal	Categorical	Change in QoL scores	T-test

VAS: visual analogue scale, PRD: pharmacy refill data, BMI, body mass index, OI: opportunistic infection, CD4: Cluster Designation 4, QoL: Quality of Life.

*** **All three measures of adherence will also be analyzed as continuous outcomes using T-test

Our Secondary endpoints will be;

• Clinical: Weight, BMI, opportunistic infections

• Biological: CD4 count, viral load

• Quality of life (QOL): Measured with the SF-12 QOL assessment form [25].

• All cause mortality

• Retention

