### Analysis plan

The analysis and reporting of the results with follow the CONSORT guidelines [28]. The statistician/data analyst will be blinded to the study group. The process of patient selection and flow throughout the study will be summarized using a flow-diagram. The analysis results of patient demographics and baseline outcome variables (both primary and secondary) will be summarized using descriptive summary measures: expressed as mean (standard deviation) or median (minimum-maximum) for continuous variables and number (percent) for categorical variables. We will adopt an intention-to-treat principle to analyze all outcomes, meaning that data from participants will be analyzed according to the group to which they were randomized even if they do not receive the allocated intervention. We will also use multiple-imputation [29] to handle missing data. We will use the T-test for comparing groups on continuous outcomes and the chi-squared test for binary outcomes. All statistical tests will be performed using two-sided tests at the 0.05 level of significance. The Bonferroni method will be used to adjust the level of significance for testing for secondary outcomes to keep the overall level at alpha = 0.05. For all group comparisons, the results will be expressed as effect (or risk ratio for binary outcomes), corresponding two-sided 95% confidence intervals and associated p-values. P-values will be reported to three decimal places with values less than 0.001 reported as <0.001. Adjusted analyses using the following baseline covariates (age, gender, education, duration on HAART, HIV staging, nutritional status (BMI) and the presence or not of an opportunistic infection (OI)) will be performed using regression techniques to investigate the residual impact of key baseline characteristics on the outcomes. Goodness-of-fit will be assessed by examining the residuals for model assumptions and chi-squared test of goodness-of-fit. All analyses will be performed using SPSS (Statistical Package for the Social Sciences) version 16.0 for Windows.

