Adherence will be measured both as a continuous outcome (change in adherence) and as a binary outcome i.e. adherent (95% of pills taken) or non adherent (< 95% of pills taken). In literature, adherence data can be handled in a number of ways. The measures can be reported as the number of doses respected or can be combined into a composite score [21]. Even though combined measures are more correlated to clinical response, they are not very practical [22]. The data from the various adherence measures will not be merged. We will report the effects of the intervention on all the measures of adherence used, and compare them for discrepancies.

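### Continuous outcomes are tested as unadjusted change from baseline, a valid method that is less precise than adjusting the follow-up value for its own baseline, and that over-corrects chance imbalance when the baseline slope is below 1

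*Protocol article*

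**What the plan says.** Table 1 of the protocol article gives a measure and a test for each outcome. Six secondary rows are changes from baseline with a t-test: weight ("Change in weight"), BMI, CD4 count ("Change in CD4 count"), viral load ("Change in viral load"), satisfaction with care, and quality of life ("Change in QoL scores").

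The Analysis plan states the general rule: "We will use the T-test for comparing groups on continuous outcomes and the chi-squared test for binary outcomes". It then says of adherence: "Adherence will be measured both as a continuous outcome (change in adherence) and as a binary outcome". The Table 1 footnote assigns the continuous adherence measures a t-test but does not itself say whether the value tested is a change.

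The Analysis plan also announces regression: "Adjusted analyses using the following baseline covariates (age, gender, education, duration on HAART, HIV staging, nutritional status (BMI", a list that closes with opportunistic infection. Baseline weight, CD4 count, viral load, satisfaction, quality of life and adherence are not in it. Baseline BMI is. The stated purpose is to explore the residual influence of baseline characteristics, so these models supplement the t-tests and do not replace them.

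The Secondary objectives place the comparisons at 3 and 6 months. Outcomes are assessed at baseline and at both visits (Duration).

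**The concern.** A change score subtracts the whole baseline value, which fixes the slope of follow-up on baseline at 1. When the true slope is smaller, the subtraction adds noise. It also means that an arm which starts low by chance appears to improve through regression to the mean. Fitting the slope from the data targets the same treatment effect without either cost.

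The setting makes both costs relevant. The Randomization section describes random blocks and mentions no stratification. Recruitment draws on patients with at least a month of treatment and on a large pool of established patients, so baseline CD4 count, viral load and adherence may vary widely. The Analysis plan applies a Bonferroni correction to the secondary outcomes, and the trial was sized only for the binary adherence outcome. At stake is the precision of the clinical, biological and quality-of-life results, and how they read if the arms differ at baseline.

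**Working it through.** **The plan's own figure.** The Sample size section gives 82 per group for 80% against 60%, two-sided 0.05, power 80%, chi-squared. With pooled variance and no continuity correction:

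n = [1.96·√(2·0.7·0.3) + 0.842·√(0.8·0.2 + 0.6·0.4)]² / 0.2² = 81.2, so 82 per group (power 80.4%).

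The figure reproduces. It concerns the binary outcome only. The documents give no power figure for any continuous outcome.

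**Variance per patient.** Let s0 and s1 be the baseline and follow-up SDs and r their correlation.

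- Change score: s0² + s1² − 2·r·s0·s1
- Follow-up value adjusted for baseline: s1²·(1 − r²)
- Difference between them: (s0 − r·s1)², which is never negative

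So in large samples the change score is never the more precise of the two. With equal SDs set to 1, the variances are 2(1 − r) and 1 − r², and the ANCOVA-to-change ratio is (1 + r)/2.

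**Assumptions for power.** The correlation r is not in the documents, so a range is shown. A true difference of 0.4 SD is assumed. The number per arm is 79, from 99 × 0.8 = 79.2 (99 per group and 20% attrition, Sample size section). The Analysis plan names Bonferroni without a divisor; 9 is assumed here, the count of secondary rows in Table 1. Power is by noncentral t with standard error √(2·variance/79).

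| r | Change variance | ANCOVA variance | Ratio | Power at 0.05, change → ANCOVA | Power at 0.05/9, change → ANCOVA |
|---|---|---|---|---|---|
| 0.3 | 1.40 | 0.91 | 0.65 | 56% → 75% | 25% → 43% |
| 0.5 | 1.00 | 0.75 | 0.75 | 70% → 82% | 39% → 54% |
| 0.7 | 0.60 | 0.51 | 0.85 | 90% → 94% | 67% → 76% |
| 0.9 | 0.20 | 0.19 | 0.95 | about 100% both | about 100% both |

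**Unequal SDs.** With s1/s0 from 0.8 to 1.25 and r from 0.5 to 0.9, the change-score variance is 1.02 to 1.75 times the ANCOVA variance, never below 1.

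**Chance imbalance.** The slope of follow-up on baseline is b = r·s1/s0. The change score subtracts the full imbalance instead of b times it, so its estimate shifts by −(1 − b) × imbalance. With equal SDs and an imbalance of 0.2 SD, the shift is −0.14, −0.10, −0.06 and −0.02 SD at r = 0.3, 0.5, 0.7 and 0.9. A simulation of 20,000 trials at r = 0.5 agreed: variance ratio change/ANCOVA 1.32 (theory 1/0.75 = 1.33), slope of the estimate on the imbalance −0.49 for change and about 0 for ANCOVA, and both estimates centred on the truth over all randomizations.

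**The case against.** The strongest reply is that nothing here is invalid. A t-test on change keeps its type I error and is unbiased over randomizations. That stands. A reader might infer that the planned secondary results would be biased or wrong; the documents do not support this. The loss is one of precision, and of the estimate's behaviour in a particular trial where the arms happen to differ at baseline.

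The size is also open. Neither r nor the 0.4 SD difference comes from the documents, and a figure at r = 0.5 alone would flatter the case. At r = 0.7 the gain is 4 points at 0.05 and 9 points at 0.05/9, and at r = 0.9 it is practically nil. Where values track closely over six months, as weight and BMI may, little is gained.

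Over-correction is not universal. It needs a chance imbalance and a slope below 1. If the follow-up SD is larger, for example s1/s0 = 1.25 with r = 0.9, the slope is 1.125 and the change score under-corrects, though it remains less precise.

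It is fair, too, that the footnote to Table 1 does not call continuous adherence a change, so for that outcome the point rests on the Analysis plan text.

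The planned regressions answer the point only for BMI, whose own baseline is listed; that baseline is also a partial proxy for weight. An article may leave model detail to a fuller document, but this one prints both the test and the covariate list, so the criticism is of a stated choice and not of an omission.

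**Conclusion.** The point holds as one of efficiency and robustness, for the six continuous secondary outcomes and the supplementary continuous adherence analysis, at both visits. With equal SDs the baseline-adjusted variance is 65% to 95% of the change-score variance for r from 0.3 to 0.9. In power, under the assumed 0.4 SD, 79 per arm and divisor 9, the gain runs from 19 points at 0.05 and 18 points at 0.05/9 (r = 0.3) to practically none (r = 0.9).

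It would be tempting to read this as a weakness in the trial's main result. It is not: the primary outcome is binary adherence by visual analogue scale, tested by chi-squared, and neither that test nor the sample size depends on the change scores. The change is worth making because it is free and because it should be fixed before the groups are compared.

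**What to change.** In Table 1 and the Analysis plan, replace the t-test on change by a linear model (ANCOVA) of the follow-up value on arm, with the same outcome's baseline value as covariate. Apply it at 3 and at 6 months to weight, BMI, CD4 count, viral load (on a suitable scale such as log10), satisfaction with care, quality of life and continuous adherence. Report the adjusted mean difference with its 95% confidence interval. Align the Table 1 footnote with the Analysis plan, so that continuous adherence has one definition. Where the further covariate-adjusted models are kept, add each outcome's own baseline to their list.

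The cost is a change of wording. The plan already provides for baseline assessment, regression and suitable software, so no extra patients, visits or measurements are needed.

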### Participants: inclusion/exclusion criteria

We will include subjects who are aged above 21 years, own a mobile phone and can read text messages, and who have been on HAART for at least a month. Informed consent is a prerequisite for participating in the study, and will be provided orally and in writing.

We will exclude participants who have been on HAART for less than a month, are aged less than 21 years. Participants who have used HAART for at least one month are chosen so that we can calculate a baseline figure for adherence.

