### Sample size

The sample size calculation is based on the test of the null hypothesis that the rates of adherence to HAART in the two groups (intervention and control) are equal. The primary measure of effect is the rate of adherence to ART treatment as measured by using the VAS over 6 months. The criterion for significance (alpha) has been set at 0.05. The test is 2-tailed, which means that an effect in either direction will be interpreted. The sample size was calculated using the WINPEPI (PEPI- for-windows) version 9.5 software [26]. With the proposed sample size of 82 in each of the two groups (i.e. assuming a 1:1 allocation ratio), the study will have power of 80% to yield a statistically significant result using a chi-squared test (assuming an intention-to-treat principle for the analysis) of the relative risk at alpha = 0.05. This computation assumes an adherence rate of 80% (for the intervention group) versus 60% (for the control group) at 6 months. These estimates are reflective of estimates from similar studies investigating SMS effect on drug adherences [27] and were modified to account for the type of intervention and patients for this study. We adjusted the sample size for a potential attrition rate of 20% (due to drop-outs) based on attrition rates to care in this centre. Therefore, the required sample size is 198 patients (99 per group). At the YCH ATC, on average, there are about 120 patients put on HAART per month. We estimate that about 90% will have mobile phones and would be eligible to participate in the study. Of these, it is expected that approximately 75% would be willing to participate in the study and will provide consent to participate in the trial. The expected period for recruitment will be one month to obtain 198 patients needed for the trial. It is feasible to recruit 198 patients in one month because we will also recruit from the large pool of old patients. Our study is designed to detect a 20% increase in adherence.

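### Viral load is set as untransformed change compared by T-test, which would probably miss a real difference that a log10 or suppression analysis of the same samples could detect

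*Protocol article*

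**What the plan says.** The list of secondary endpoints under Table 1 includes "Biological: CD4 count, viral load". The Table 1 row for viral load is filled in completely: scale ratio, type continuous, measure "Change in viral load", method T-test. The Analysis plan repeats the rule: "We will use the T-test for comparing groups on continuous outcomes and the chi-squared test for binary outcomes". No log10 scale, assay limit or suppressed/not suppressed outcome is named anywhere.

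The adjusted analyses in the Analysis plan use age, gender, education, duration on HAART, HIV staging, BMI and opportunistic infection. Baseline viral load is not in that list. On multiplicity, the same section states: "The Bonferroni method will be used to adjust the level of significance for testing for secondary outcomes".

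The population is broad. The eligibility section admits patients "who have been on HAART for at least a month", and the Sample size section adds that "we will also recruit from the large pool of old patients".

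**The concern.** Viral load is usually strongly right-skewed, and here the skew is compounded by the recruitment. Patients one month into treatment may still be falling from high values, while many long-treated patients may sit at the assay limit at both visits. Change in copies is then near zero for many participants and very large for a few. Those few set the variance that the T-test divides by. Values below the assay limit also have no exact number, so their change is not defined without a rule.

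The Background links poor adherence to poor virological response, and the primary measure is a patient-rated scale. Viral load is therefore one of the laboratory outcomes that could support or question the primary result. If its planned analysis has little power, a null finding would say little either way.

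**Working it through.** **Inputs from the protocol.** 82 per group before attrition; "The criterion for significance (alpha) has been set at 0.05"; two-sided testing; Bonferroni for secondary outcomes. Table 1 has nine secondary rows, so 0.05/9 = 0.0056 if each is counted once (the count is an assumption).

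**Inputs assumed, because the protocol gives none for viral load.** Suppression at 6 months of 80% v 60%, borrowed from the adherence rates; detectable values log-normal with mean 3.5 to 4.5 and SD 0.3 to 1.0 on the log10 scale; floor of 50 copies.

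**Step 1: the plan's own figure.** For a chi-squared test of 80% v 60%:

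n = [1.96 × √(2 × 0.7 × 0.3) + 0.8416 × √(0.8 × 0.2 + 0.6 × 0.4)]² / 0.2² = 81.2, rounded up to 82 per group.

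This reproduces the protocol. Power with 82 is 80.4% at 0.05. At 0.0056 (z = 2.773) it is Φ[(0.2√82 − 2.773√0.42)/√0.40] = 50.9%. A suppression comparison with these rates would have the same power.

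**Step 2: why the scale matters.** Take the simple case where everyone is suppressed at baseline. Change is then about zero for those still suppressed and about X, the detectable value, for the rest. Write k = E(X²)/E(X)² = exp[(s ln 10)²], where s is the log10 SD. In units of the mean of X:

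- difference between arms = 0.4 − 0.2 = 0.2
- variances = 0.4k − 0.16 (control) and 0.2k − 0.04 (intervention)

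| s | k | SE of difference (82 per arm) | 0.2/SE |
|---|---|---|---|
| 0.3 | 1.61 | 0.097 | 2.07 |
| 0.5 | 3.76 | 0.158 | 1.26 |
| 0.8 | 29.8 | 0.464 | 0.43 |
| 1.0 | 201 | 1.211 | 0.17 |

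The suppression difference is the same in every row; only the spread of the detectable values changes. The normal approximation gives power of 54% at s = 0.3 and 7% at s = 0.8. Simulation gives 56% and 15% for the same case. The approximation is rough with heavy tails, but the direction is clear.

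**Step 3: simulation over baseline mixes.** 82 per arm, about 1,500 to 2,000 runs per scenario, two-sided 0.05:

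| Baseline assumption | Change, untransformed | Change, log10 | Follow-up value, log10 | Proportion suppressed |
|---|---|---|---|---|
| No recent starters, status independent of follow-up | 7-27% | 40-46% | 70-80% | 78-81% |
| 30% recent starters | 3-8% | 28-42% | 71-79% | 80-82% |
| All recent starters | 3-5% | 50-65% | 73-82% | 81-83% |
| Suppressed patients stay suppressed | 7-72% | 99% or more | 75-78% | 80-83% |
| All detectable at baseline | 6-32% | 62-77% | 73-79% | 79-82% |
| All suppressed at baseline | 9-56% | 73-80% | 73-80% | 80-82% |

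Recent starters were given a baseline mean of 4.8 and SD of 0.7 log10. Untransformed change had less power than the suppression comparison in all 27 scenarios, and less than 50% power in 25 of them. With s of 0.8 to 1.0 it never exceeded 15%.

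**Step 4: at 0.0056.** Untransformed change has 0.1-38% power (at most 1.4% with s of 0.8 to 1.0). The suppression comparison has 49-55% here, and 46% in a separate run with 79 per arm and 40% recent starters.

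**Step 5: dominance, baseline adjustment and false positives.** In that separate run, 5 of 158 patients supplied about 92% of the total sum of squares of untransformed change in the median trial. At 0.05, power was 3% for untransformed change, 71% for log10 viral load adjusted for baseline and 78% for suppression. Another run with 79 per arm and s from 0.9 down to 0.3 gave 4-25%, 74-79% and 78-80%. With no true effect, the T-test on untransformed change rejected in about 2-3% of trials, so it is conservative.

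**The case against.** The strongest reply is that untransformed is inferred from silence. Table 1 is an overview with a few words per row, and a log10 scale and a rule for values below the assay limit could sit in an analysis plan that is not shown. That would be decisive if the row left the method open. It does not: it states scale, type, measure and test, and the Analysis plan repeats the test. If log10 was intended, the row misdescribes it and still needs correcting.

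Several limits on the point do stand:

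- A reader might infer that a real difference would almost surely be missed. The protocol gives no viral load mean, SD, suppression rate or target difference, so this cannot be derived. Across the scenarios the chance of a miss at 0.05 runs from about 28% to 97%.
- Part of the low power comes from the Bonferroni level, not the scale. Even the suppression comparison falls to about 51% at 0.0056.
- A reader might take viral load to be the only outcome free of self-report. CD4 count, weight, BMI, mortality, retention and pharmacy refill are also listed.
- The adjusted analyses already include duration on HAART and a check of residuals. They do not include baseline viral load, and they do not change the scale.
- A log10 scale alone is not a full remedy. The T-test on log10 change ranged from 28% to over 99% with the baseline mix, so its rank against the suppression comparison is not fixed.
- Randomisation balances baseline level and treatment duration in expectation. The issue is efficiency, not bias.

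**Conclusion.** The point holds as a weakness in a stated method. As written, the viral load comparison is a T-test on untransformed change, and in this mixed population it would probably miss a real difference. The direction of the loss against a suppression comparison was the same in every scenario tried. Its size depends on the assumed spread and baseline mix: slight in the most favourable case (72% against 80%) and nearly total where the spread is wide or recent starters are included. All figures assume suppression of 80% v 60% and log-normal detectable values, and the Bonferroni figures also assume nine tests. The primary outcome, its sample size and its conclusion are unaffected. The change should be made, but the trial does not stand or fall on it.

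**What to change.** Replace the Table 1 row for viral load with two analyses of the same samples:

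1. log10 viral load at 6 months, compared by regression adjusted for baseline log10 viral load and duration on HAART (already a listed covariate), with values below the assay limit set to the limit or treated as censored;
2. the proportion below the assay limit at 6 months, reported as a risk ratio with its 95% confidence interval.

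State in the Analysis plan which of the two is the Bonferroni-counted test, and add baseline viral load to the covariates for this outcome.

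The cost is one table row and a sentence or two of text, with no extra blood tests or patients. The downsides are small: the dichotomised result discards information above the limit, and one more analysis is reported.

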### Duration

The trial will run for six months, with outcome assessment at baseline, 3 months and 6 months.

